### Data analysis for the economic evaluation

The economic evaluation will be conducted as a cost-effectiveness analysis. A health sector viewpoint will be taken to estimate the costs of all activities and resource use related to the study participants’ disease. T1 will be taken as the start of the time frame that will end at T4. All costs will be reported in 2015-Euros. By the use of register data to estimate costs, we expect a full follow-up of these data. The method of multiple imputation [58] will be used to handle possible lost to follow-up in the ADL motor ability or the EQ-5D-5L due to other reasons than death.

In the cost-effectiveness analysis the ADL motor ability will be used as the clinical parameter and QALY will be used as the measure of utility. In order to calculate QALY the EQ-5D-5L the recommended standard mapping procedure will be used based on the Danish preference weights [45]. The QALYs over 24 weeks will be calculated by interpolation of the area under the curve with four time points (T1, T2, T3, and T4). The resource use, costs, and clinical outcome will be presented as means with 95 % bootstrapped confidence intervals (10,000 replicates) [62]. The Incremental Cost-Effectiveness Ratio (ICER) will be calculated using the formula: ICER = (C_A_ – C_B_) / (E_A_ – E_B_), where C denotes costs and E denotes effects with A and B referring to comparators. The ICER summarises the results of each economic evaluation in a single parameter, defined as the ratio of additional costs per additional unit of effect [53]. The ICER is, however, undefined if the ratio or just one of the confidence limits is negative.

The result of the cost-effectiveness analysis will be summarised in cost-effectiveness acceptability curves (CEAC) [63]. A CEAC is a graphic representation of the uncertainty in cost differences and effect differences between the two groups [63]. To deal with the structural uncertainties, sensitivity analysis will be performed to test the influence of the chosen imputation strategy. Further sensitivity analysis will be performed to test the inclusion of productivity costs and patients’ out-of-pocket payments [53].

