**Fig. 1 Fig1:**
[figure not shown]
Randomisation and data collection

**Table 1 Tab1:** Schedule for collection of outcomes and cost data

Outcome	Source	Data collection method	Baseline T1	Week 6 T2	Week 12 T3	Week 24 T4
Everyday activities						
Quality of ADL performance	AMPS	Observation	X		X	
Problems with everyday activities	IPPA	Structured interview	X	X	X	
Autonomy and participation	IPA-DK	Questionnaire	X	X	X	
Health-related Quality of Life						
Health-related quality of life	EORTC QLQ C-30	Questionnaire	X	X	X	
Economic evaluation						
Quality Adjusted Life Years (QALY)	EQ-5D-5L	Questionnaire	X	X	X	X
Intervention costs		Questionnaire		X		
Costs in the secondary health care sector	The National Patient Registry	Register	X	X	X	X
Costs in the primary healthcare sector	The Danish National Health Service Register for Primary Care	Register	X	X	X	X
Prescriptive medication	Danish Register of Prescriptive Medication	Register	X	X	X	X
Out-of-pocket costs		Cost diary	X	X	X	X
Productivity costs	The Danish Register for Evaluation of Marginalization	Register and questionnaire	X	X	X	X

*AMPS* The Assessment of Motor and Process Skills, *EORTC QLQ-C30* The European Organization for Research Treatment of Cancer Quality of Life Questionnaire Core 30, *EQ-5D-5L* The EuroQol 5-dimensions 5 levels, *IPA-DK* The Danish version of the Impact on Participation and Autonomy Questionnaire (IPAQ), *PPA*, The Individually Prioritised Problems Assessment

There will be three follow-up occasions where cost data from registers are also extracted, while demographic data are only collected at T1:

T2) Six weeks after T1: a postal questionnaire identical to the one sent out at T1 and a study specific questionnaire on the type of interventions both groups have received and/or completed. Besides, an IPPA telephone interview is accomplished.

T3) 12 weeks after T1: identical to T1 except that a question whether their everyday life has improved is also asked.

T4) 24 weeks after baseline: a postal questionnaire that includes the cost diary and the EQ-5D-5L.

Observation based data are collected in conjunction with the intervention, and qualitative interviews with a subsample are accomplished at T3.

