## Randomisation

Study participants will be randomly assigned to either the intervention group (receiving the Cancer Home-Life Intervention as a supplement to usual care) or the control group (receiving usual care and not receiving the Cancer Home-Life Intervention). See Fig. 1.

Randomisation will be carried out after T1 by an administration office, which is independent of the trial. Participants will be randomly assigned in a preset block size to either the intervention or control group with a 1:1 allocation by a computer-generated randomisation schedule. The block size will be kept unknown to all investigators and P-OTs and will not be revealed until the study has ended. The randomisation is stratified by centre.

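### QALYs include the pre-randomisation T1 utility, and the described comparison has no adjustment for it, so the incremental QALY and ICER carry any chance T1 imbalance and are less precise than they could be

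*Protocol article*

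**What the plan says.** All places are in the protocol article.

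- **Time frame** (Data analysis for the economic evaluation): "T1 will be taken as the start of the time frame that will end at T4".
- **QALY construction** (same section): "The QALYs over 24 weeks will be calculated by interpolation of the area under the curve with four time points", namely T1 to T4.
- **Visit times** (text below Table 1): T2 is "Six weeks after T1: a postal questionnaire identical to the one sent out at T1", T3 is "12 weeks after T1: identical to T1" and T4 is "24 weeks after baseline: a postal questionnaire that includes the cost diary and the EQ-5D-5L". Table 1 schedules the EQ-5D-5L at all four.
- **Order of events** (Randomisation): "Randomisation will be carried out after T1 by an administration office".
- **Presentation** (economic section): "The resource use, costs, and clinical outcome will be presented as means with 95 % bootstrapped confidence intervals", with 10,000 replicates. The ICER is the cost difference divided by the effect difference, and uncertainty is summarised in acceptability curves.
- **Economic sensitivity analyses**: the imputation strategy, productivity costs and out-of-pocket costs. None concerns baseline utility.
- **Covariates** (Data analyses of the clinical evaluation): all outcomes are adjusted for centre. Other baseline variables are considered only after significant imbalance and only in a sensitivity analysis. That list includes the EORTC global health score but not EQ-5D utility.

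**The concern.** T1 utility cannot reflect treatment, yet it enters the QALY in two ways: directly, as the first point of the area, and indirectly, because people with higher utility at T1 tend to have higher utility later. With no adjustment, a chance T1 difference between arms passes into the incremental QALY. That quantity is small over 24 weeks and is the denominator of the ICER, so modest shifts matter. Two of the four stated hypotheses, on QALYs gained and on cost-effectiveness, rest on it.

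The covariate rule in the clinical section does not solve this. It sits under a different heading, is triggered by a significance test that would miss an ordinary one-SE imbalance, leads only to a possible sensitivity analysis, and omits EQ-5D utility.

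**Working it through.** The protocol gives no precision figure for QALYs, so there is none to reproduce. The 136 per arm comes from Sample size (92 / 0.68 = 135.3, rounded up).

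**1. Weights, from the visit times alone.** With linear interpolation between weeks 0, 6, 12 and 24, the trapezoid weights are:
- T1: 6/2 = 3 weeks
- T2: 12/2 = 6 weeks
- T3: (24 − 6)/2 = 9 weeks
- T4: 12/2 = 6 weeks

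They sum to 24 weeks. T1 makes up 3/24 = 12.5% of the area, or 3/52 = 0.0577 QALY per unit of utility. T2 to T4 together weigh 21/52 = 0.4038.

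**2. Assumptions not in the protocol.** Utility SD 0.20, and an equal correlation ρ between visits of 0.5 to 0.7 (0.3 as a lower case).

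**3. Slope of QALY on T1 utility if all survive.** Slope = 0.0577 + ρ × 0.4038:
- ρ = 0.3: 0.179
- ρ = 0.5: 0.260
- ρ = 0.7: 0.340

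**4. Size of an ordinary imbalance.** SE of the T1 difference = 0.20 × √(2/136) = 0.0243. The shift in incremental QALYs per one-SE imbalance is slope × 0.0243 = 0.0043, 0.0063 and 0.0083 for the three correlations.

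**5. Yardstick.** A utility gain of 0.05 held from T2 to T4 gives 0.05 × 0.4038 = 0.020 QALY.

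**6. Precision if all survive.** The correlation r between T1 utility and the QALY is 0.70 at ρ = 0.5 and 0.83 at ρ = 0.7. The adjusted-to-unadjusted SE ratio is √(1 − r²) = 0.71 and 0.55. At ρ = 0.5 the SE falls from 0.0090 to 0.0064 QALY.

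**7. Allowing for deaths.** The Discussion expects that a substantial part of the sample may have died by T4, and reports that 10 of 84 participants from one hospital in the earlier study were alive one and a half years (78 weeks) after it ended. A constant hazard gives (10/84)^(24/78) = 0.52 at 24 weeks. That study also enrolled WHO status 3, so survival here may be higher, and 52-90% is used as the range. Simulation with mean utility 0.65, zero utility after death, exponential survival and death independent of T1 utility gives:

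| Survival to week 24 | SE ratio, ρ = 0.5 | SE ratio, ρ = 0.7 | Shift per one-SE imbalance (QALY) |
|---|---|---|---|
| 90% | 0.83 | 0.73 | 0.006-0.008 |
| 80% | 0.88 | 0.81 | 0.006-0.007 |
| 70% | 0.91 | 0.86 | 0.005-0.007 |
| 52% | 0.94 | 0.90 | 0.005-0.006 |

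If lower T1 utility also predicts death (hazard about 1.6 times as high per SD lower), the SE ratio falls to 0.68 at 90% survival with ρ = 0.7. The shift then rises to between 0.009 and 0.010 at 52% survival with ρ = 0.7. Overall, the SE ratio is about 0.68-0.94 and the shift about 0.005-0.010 QALY, which is 25-50% of the 0.020 yardstick.

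**The case against.** **The article never says unadjusted.** This is true. The ICER formula would fit adjusted effects as well, and the sentence on means refers to clinical outcome, whereas the same section calls the QALY the measure of utility. A fuller economic plan could add the adjustment. What remains is that the article goes well beyond generalities: it fixes the QALY construction, bootstrap, replicate number, ICER and sensitivity analyses, and T1 utility has no role in any of them except inside the outcome. The point is a better method at almost no cost, not a complaint about missing detail.

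**A reader might infer that the plan is biased.** The protocol does not support that. T1 precedes randomisation, so T1 differences are chance, the unadjusted difference is unbiased on average, and the bootstrap interval and acceptability curve already include this variability. Only the sensitivity of the realised estimate and the lost precision stand.

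**A reader might take 55-71% as the expected SE ratio.** That assumes no deaths, against the protocol's own expectation. Deaths add variation that T1 utility explains only in part, so the likely gain is smaller.

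**A reader might say that QALYs are not adjusted for centre.** That is too flat. The clinical section adjusts all outcomes for centre, and the EQ-5D-5L is listed under health-related quality of life, a secondary outcome. Whether the rule reaches QALYs is open, because it stands under the clinical heading.

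**It touches only the economic evaluation.** This is correct. The primary outcome and sample size are unaffected.

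**Conclusion.** The point holds as a free improvement to the economic analysis. As described, the incremental QALY and ICER carry any chance T1 utility difference, and neither the economic sensitivity analyses nor the clinical covariate rule deals with it.

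The 12.5% direct weight of T1 follows from the visit schedule and linear interpolation alone. All other sizes rest on the assumed SD, correlations, mean utility and survival. The shift in the point estimate is the firmer result, since it changes little when deaths are allowed for. The precision gain is less certain: it could be substantial with high survival and strong correlation, and as little as about 6% of the SE at 52% survival. The point does not show systematic bias or invalid intervals.

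**What to change.** State in the economic section that the incremental QALY is estimated by regression on arm, T1 EQ-5D-5L utility and centre. Make explicit that the centre adjustment in the clinical section extends to QALYs. Take the adjusted difference within each of the 10,000 bootstrap replicates and use it in the ICER and the acceptability curve. Keep the raw group means as descriptive output.

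The cost is a sentence or two in the plan and a small change to the analysis code. T1 EQ-5D-5L is already collected, and no visit, instrument or sample size changes. Fixing this before unblinded data are seen also avoids a later choice between adjusted and unadjusted ICERs.

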## Analysis

### Data analyses of the clinical evaluation

Scores will be calculated following the instructions in each instrument manual and presented by descriptive statistics. The intervention group will be compared with the control group by means of a multiple linear regression analysis in continuous data (AMPS, EORTC QLQ C-30 and IPPA), given the assumptions are fulfilled. If the assumptions are not met, a relevant transformation or logistic regression will be used. IPA-DK data are ordinal and will be dichotomised before logistic regression analysis is applied. The analysis of all outcomes will be adjusted for the stratification variable, centre. If there is significant imbalance between the two groups we shall consider adjusting for baseline ADL motor ability, baseline ADL process ability, gender, age, primary cancer diagnosis, education, employment and the EORTC QLQ-C30 global health status/quality of life in a sensitivity analysis [55, 56]. The between-group differences in continuous and dichotomised data will be presented with 95 % confidence intervals. A complete case analysis excluding participants without post-randomisation data will be performed [57]. It will be supplemented with a sensitivity analysis applying multiple imputation used to estimate a plausible value for the missing data of study participants lost to follow-up of other reasons than death [58].

Analyses will be performed to identify groups in which the Cancer Home-Life Intervention is especially effective. A subgroup-treatment effect interaction by a multiple regression analysis will be performed with the following possible variables as effect modifiers: age, gender, primary cancer diagnosis and WHO Performance score [59, 60].

*P* values ≤0.05 will be considered statistically significant. Analyses will be performed using STATA.

The One Day Diary data from T1 and T3 will be coded thematically into the following structure: 1) The activity domain comprising seven categories: self-care; care for others; household; leisure; transportation; procurement and preparation of food; and work. 2) The geographical domain: location and movements. 3) The social context: social circle and interaction. 4) The experiential domain: physical state and state of mind. The analyses will be used to describe the study participants’ daily activities with regard to each domain including duration and frequency of activities as well as activity patterns for the individual over the time of a day [47].

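### As stated, the incremental cost is a difference in group means with no covariate, although costs are collected at T1 and randomisation is stratified by centre; precision is lost and chance imbalance in prior resource use is left in

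*Protocol article*

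**What the plan says.** All references are to the protocol article.

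- *Data analysis for the economic evaluation* gives the reporting format: "The resource use, costs, and clinical outcome will be presented as means with 95 % bootstrapped confidence intervals (10,000 replicates". It defines the ICER as (C_A − C_B)/(E_A − E_B), "where C denotes costs and E denotes effects with A and B referring to comparators", and summarises uncertainty in an acceptability curve. No covariate is named for cost.
- The same section fixes the costing window: "T1 will be taken as the start of the time frame that will end at T4". Its sensitivity analyses cover the imputation strategy and two further cost components: "Further sensitivity analysis will be performed to test the inclusion of productivity costs and patients’ out-of-pocket payments". Neither T1 cost nor centre appears among them.
- Table 1 marks secondary care, primary care, prescription, out-of-pocket and productivity costs at baseline as well as at weeks 6, 12 and 24, for example "Costs in the secondary health care sector The National Patient Registry Register X X X X". The text below the table adds: "There will be three follow-up occasions where cost data from registers are also extracted, while demographic data are only collected at T1".
- *Randomisation* takes place after T1, and "The randomisation is stratified by centre".
- *Data analyses of the clinical evaluation* states: "The analysis of all outcomes will be adjusted for the stratification variable, centre". Its list of covariates to consider under imbalance contains no cost variable.

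**The concern.** The clinical section names a regression model, the stratification factor and a conditional covariate list. The economic section is just as specific about its own method (means, 10,000 bootstrap replicates, the ratio formula, the acceptability curve, the sensitivity analyses), and none of that involves a covariate. The natural reading is that incremental cost is a difference in unadjusted group means. The T1 cost data then have no stated role in the analysis.

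If resource use before T1 predicts resource use after it, which is plausible in advanced cancer but not quantified in the article, two things follow. The interval for incremental cost is wider than it need be. And if one arm happens to contain more heavy users, part of that excess appears in the incremental cost. Two of the stated hypotheses depend on this quantity: more QALYs at a higher incremental cost, and cost-effectiveness in a health sector perspective. If an imbalance is seen, the article offers no prespecified remedy for costs, so any adjustment made then would be post hoc.

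**Working it through.** **Inputs.** *Sample size* gives 92 per group evaluable, 136 per group enrolled, and 32% dropout at 12 weeks. The economic section expects full follow-up of register costs, so 136 per arm is the relevant number for cost. The correlation ρ between T1 cost and T1–T4 cost is not given; 0.1, 0.3, 0.5 and 0.7 are assumed.

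**The plan's own figures.** There is no cost SD, cost difference or cost correlation to reproduce. The enrolment figure does reproduce: 92/(1 − 0.32) = 135.3, so 136 per arm and 272 in total.

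**Size of a chance imbalance.** In units of the T1 cost SD, the standard error of the between-arm difference is √(2/136) = 0.121. The 95% range is ±1.96 × 0.121 = ±0.238 SD. The probability of a difference above 0.2 SD in either direction is 2 × [1 − Φ(0.2/0.121)] = 0.099, about one trial in ten.

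**Effect of adjustment.** A T1 imbalance of 0.2 SD carries ρ × 0.2 SD into the unadjusted incremental cost. Adjusting for T1 cost multiplies the standard error by √(1 − ρ²). The unadjusted 95% half-width is 0.238 SD.

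| ρ (assumed) | carried from 0.2 SD | √(1 − ρ²) | adjusted half-width (SD) | interval narrower by |
|---|---|---|---|---|
| 0.1 | 0.02 SD | 0.995 | 0.236 | 0.5% |
| 0.3 | 0.06 SD | 0.954 | 0.227 | 5% |
| 0.5 | 0.10 SD | 0.866 | 0.206 | 13% |
| 0.7 | 0.14 SD | 0.714 | 0.170 | 29% |

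**Check with skewed costs.** Lognormal costs were simulated with 136 per arm, no true cost effect and 4,000 runs per setting. Both the unadjusted and the adjusted difference centred on zero within simulation error. With log-scale correlations of 0.3, 0.5 and 0.7 (ordinary correlations of about 0.20, 0.38 and 0.59), the SD of the adjusted estimate was 0.97, 0.92 and 0.78 times that of the unadjusted one. The formula at those ordinary correlations gives √(1 − 0.20²) = 0.98, √(1 − 0.38²) = 0.92 and √(1 − 0.59²) = 0.81, so it remains a fair guide under skewness.

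**Centre.** The gain from adding centre depends on the cost difference between the two hospitals, which the article does not give.

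**The case against.** The strongest reply is that the article nowhere calls the means unadjusted. A bootstrapped mean is a reporting format, the ICER formula holds equally for adjusted means, and a condensed article may leave covariates to a plan that is not shown. This stands in part: the point concerns the method as stated, and a fuller plan could already contain the adjustment. But the economic section describes its method in some detail, and the T1 cost data have no role in it.

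Three further objections stand.

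- **Centre is unclear rather than absent.** The adjustment of all outcomes for centre sits under the clinical heading. It covers ADL motor ability, the clinical effect in the ICER, but it is not evident that it covers costs. How the bootstrap treats centre is not stated either way.
- **T1 cost is not yet a defined variable.** No look-back period is given, and T1 is also the start of the costing window, so the T1 mark in Table 1 could mean only that the window opens there. The sentence about extraction at the follow-ups as well favours a separate baseline extraction but does not settle it.
- **The correlation may be low.** The *Discussion* warns that a substantial part of participants may not be alive at T4, and death could weaken the link between prior and later cost.

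A reader might infer that the planned cost difference is biased. The documents do not support that: under 1:1 randomisation it is unbiased, and the bootstrap interval and acceptability curve already express chance imbalance. A reader might also translate the precision gain into power by borrowing the sample-size section's 92 per group and 0.3 logits. Those belong to the ADL motor outcome after dropout. Register costs are expected for all 136 per arm, and no powered cost test is planned, so a power comparison has no basis here.

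**Conclusion.** The point holds as one of efficiency and prespecification. The stated incremental cost is valid but less precise than the trial's own data could allow, and it leaves any realised imbalance in prior resource use in the ICER and the acceptability curve. The gain runs from negligible (interval 0.5% narrower at ρ = 0.1) to substantial (29% at ρ = 0.7). It rests on an assumed correlation, full register follow-up of 136 per arm, and a T1 cost that genuinely precedes the costing window. It concerns the economic aim only; the primary clinical comparison is unaffected. The change is worth making because it is cheap and should be fixed before the data are seen.

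**What to change.** In *Data analysis for the economic evaluation*:

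1. Estimate incremental cost by regressing T1–T4 cost on arm, centre and T1 cost.
2. Define T1 cost as the same register items over one fixed look-back period ending at T1, so that it does not overlap the costing window.
3. Bootstrap within arm and centre, refitting the regression in each replicate.
4. Use the adjusted cost difference in the ICER and the acceptability curve.
5. Keep the unadjusted means with bootstrapped intervals as description.

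The cost is a few sentences of analysis wording and some programming. No new participants or data sources are needed, since the registers are already used; if the T1 mark proves to mean only the opening of the window, the extraction dates would have to reach back further. The downsides are that a look-back period has to be chosen in advance, and that the gain is small if prior cost predicts later cost poorly.

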#### Hypotheses

The quality of ADL performance as demonstrated by motor and process ability will be better in participants undergoing the Cancer Home-Life Intervention compared to participants who receive usual care.Participants undergoing the Cancer Home-Life Intervention will report less difficulty with prioritised everyday activities, better autonomy and participation, and higher levels of health-related quality of life compared to participants who receive usual care.The Cancer Home-Life intervention provides more Quality Adjusted Life Years (QALYs) at a higher incremental cost.The Cancer Home-Life intervention is cost-effective in a health sector perspective.

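### The protocol calls the ICER undefined when it or one confidence limit is negative; this gives dominant and dominated results the same label and passes positive ratios from the cheaper-but-worse quadrant

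*Protocol article*

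**What the plan says.** The section on data analysis for the economic evaluation gives the ICER as the cost difference over the effect difference, "defined as the ratio of additional costs per additional unit of effect", and describes it as the one-number summary of each evaluation. It then adds the restriction: "The ICER is, however, undefined if the ratio or just one of the confidence limits is negative".

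The same section plans other output that does not depend on the ICER:
- "The resource use, costs, and clinical outcome will be presented as means with 95 % bootstrapped confidence intervals (10,000 replicates"
- "The result of the cost-effectiveness analysis will be summarised in cost-effectiveness acceptability curves (CEAC", with the explanation that "A CEAC is a graphic representation of the uncertainty in cost differences and effect differences between the two groups"

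The Hypotheses section contains two economic hypotheses: "The Cancer Home-Life intervention provides more Quality Adjusted Life Years (QALYs) at a higher incremental cost" and "The Cancer Home-Life intervention is cost-effective in a health sector perspective". The time frame is 24 weeks: "T1 will be taken as the start of the time frame that will end at T4".

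**The concern.** The restriction judges the ICER by its sign, and the sign does not carry the information needed. Opposite signs of the cost and effect differences give a negative ratio in the best quadrant and in the worst one. Equal signs give a positive ratio both for dearer and better (the hypothesised quadrant) and for cheaper and worse, where a large ratio is good news rather than bad.

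Applying the rule to the confidence limits adds a filter. For an intervention that improves the outcome, the ICER survives only if it is also clearly dearer. If the intervention turns out cheaper than hypothesised, the more favourable result is the one whose headline figure is withheld. At stake is a correct and unselective report of the figure that the protocol itself names as its economic summary.

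**Working it through.** **1. The formula.** ICER = (C_A − C_B)/(E_A − E_B) = dC/dE. It has no value only at dE = 0. By quadrant:

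| dC | dE | Meaning | Sign of ratio | Rule applied to the ratio |
|---|---|---|---|---|
| + | + | dearer, better | + | passes |
| − | + | dominant | − | undefined |
| + | − | dominated | − | undefined |
| − | − | cheaper, worse | + | passes |

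This step needs no assumption: every dominant point estimate is labelled undefined.

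**2. Illustration.** The document gives no cost or QALY figures, so these are assumed: standard errors 1,500 for dC and 0.012 QALY for dE, no correlation. The CEAC height at threshold λ is P(cost-effective) = Φ[(λ·dE − dC)/√(λ²·0.012² + 1,500²)].

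| Case | dC | dE | ICER | λ = 0 | 20,000 | 40,000 | 80,000 |
|---|---|---|---|---|---|---|---|
| dearer, better | 800 | 0.02 | 40,000 | 0.30 | 0.40 | 0.50 | 0.67 |
| dominant | −500 | 0.02 | −25,000 | 0.63 | 0.72 | 0.80 | 0.88 |
| dominated | 800 | −0.01 | −80,000 | 0.30 | 0.26 | 0.22 | 0.18 |
| cheaper, worse | −800 | −0.01 | 80,000 | 0.70 | 0.65 | 0.60 | 0.50 |

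For the dominant case at λ = 20,000: (400 + 500)/√(240² + 1,500²) = 900/1,519 = 0.59, and Φ(0.59) = 0.72. The CEAC separates dominant from dominated; the label does not. The first and last rows both have positive ratios, but the curve rises with λ in one and falls in the other. That is the reversal. (With standard errors this large, the limits in those two rows would also trigger the rule; the rows only show what the ratio means.)

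**3. The limits as a criterion.** With percentile limits, the lower limit is negative exactly when more than 2.5% of replicates have dC and dE of opposite sign. Changing both signs leaves the ratio unchanged, so a clearly cheaper and worse intervention passes as often as a clearly dearer and better one.

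**4. How often the rule applies.** The protocol states no figure for this, so there is none to reproduce. The one signal it fixes is for ADL motor ability, which is also the clinical effect in the economic analysis. In the Sample size section the difference is 0.3 logits, SD 0.727, 92 per group, power 80%. The check gives 93 per group by the normal formula and power 0.799 at 92, in agreement. The signal is 0.3/(0.727·√(2/92)) = 0.3/0.107 = 2.8 standard errors.

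Let zc and ze be the true cost and effect differences in standard errors. Simulation: independent normal estimates, 1,000 trials per cell, 2,000 resamples each, percentile limits. Share of trials in which the ratio or a limit is negative:

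| zc | ze = 1 | ze = 2 | ze = 2.8 | ze = 4 |
|---|---|---|---|---|
| −1 | 100% | 100% | 100% | 100% |
| 0 | 100% | 99% | 98% | 97% |
| 1 | 98% | 93% | 87% | 84% |
| 2 | 94% | 76% | 60% | 51% |
| 2.8 | 86% | 60% | 39% | 24% |
| 4 | 85% | 51% | 20% | 4% |
| 6 | 81% | 46% | 20% | 2% |

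The rule applies often when either difference is weakly estimated, and rarely when both are clear and positive. By the symmetry in step 3, at zc = ze = −4 about 96% of trials would pass with a positive ratio, although the intervention is then cheaper and worse.

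**The case against.** The restriction concerns one summary figure. Nothing in the section says that an undefined ICER ends the analysis or suppresses other output. The CEAC is planned without condition, exists in all four quadrants and needs no ratio. Mean costs and outcomes with bootstrap intervals are also presented, so a cheaper and better arm would be visible. All of this stands.

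A reader might therefore go too far by inferring that a dominant result is thrown away, or that the cost-effectiveness hypothesis would usually go unanswered. The documents do not support either reading, because the CEAC addresses that hypothesis directly.

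A reader might also infer that most realistic trials would end with the ICER undefined. One can choose inputs that give 83% to 99%: 136 per arm, cost SD EUR 8,000 to 15,000, true increment EUR 0 to 1,000, 24-week QALY SD 0.10 to 0.12, true gain 0.02 to 0.05. But the cost standard error is then SD·√(2/136), about EUR 970 to 1,820, so every assumed increment is at most about one standard error and the outcome is nearly built in. The protocol supplies none of these inputs, and it names no interval method for the ICER.

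The CEAC does not, however, repair the sentence itself. It does not state the quadrant of the point estimate, and it does not stop a dominant estimate being reported as undefined.

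**Conclusion.** The sentence is wrong as written, and the defect is minor. Without any assumption: a negative ratio is not undefined, dominant and dominated estimates receive the same label, the ICER is always withheld for a dominant point estimate, and a positive ratio with positive limits from the cheaper-but-worse quadrant passes unflagged. The frequency does rest on assumptions (independent normal estimates, percentile limits, chosen signals) and ranges from about 2% to 100%, so no single figure should be quoted. Data collection, the bootstrap, the CEAC and the clinical analysis are unaffected.

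**What to change.** Replace the sentence with: 'Cost and effect differences are reported with 95% bootstrap intervals and shown on the cost-effectiveness plane. The quadrant of the point estimate is stated, and a dominant or dominated result is reported as such. The ICER is given as a ratio only with its quadrant stated, and without confidence limits when replicates cross quadrants. Uncertainty is then conveyed by the CEAC, or by incremental net monetary benefit (λ × effect difference − cost difference), from the 10,000 replicates already planned.'

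The cost is wording only: no new data, no larger sample, no further resampling. The threshold range can be set in the full analysis plan; its absence from the article is not part of this point. The change should be made before cost data by arm are seen, so that the handling of dominance is not chosen afterwards.
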